### Adverse events (AEs) {22}

In this study, AEs are defined as any treatment-related medical events, including any treatment-related adverse and unexpected signs, symptoms, or diseases. The AEs known to follow nonpressure dressing and pressure dressing treatment include severe postoperative hemorrhage. At each visit, the participants will report AEs and be examined by a physician. AEs will be evaluated and reported to the principal investigator according to Common Terminology Criteria for Adverse Events (v4.03) [22].

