**Methods:**

In this study, we plan to include 186 patients who have undergone modified Milligan-Morgan hemorrhoidectomy, which only sutured external hemorrhoids to reduce the risk of bleeding. The purpose is to determine whether the use of nonpressure dressings after open hemorrhoidectomy is inferior to the use of pressure dressings in terms of severe postoperative bleeding and postoperative complications. The primary endpoints of the trial are the incidence of urinary retention within 24 h after surgery and the incidence of severe postoperative bleeding 1 h after dressing removal, which requires revision surgery within 24 h after the surgery. The secondary endpoints of the study are the pain score, anal distension score, postoperative use of analgesics, and incidence of medical adhesive-related skin injury, all of which will be assessed before removing the dressings. The length of hospitalization in days and hospitalization expenses will be recorded. Safety will be assessed with consideration of all adverse and severe adverse events related to the study treatment.

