#### Secondary objectives

To assess the impact of pressure dressings versus nonpressure dressings surveillance on:
Pain score within 25 h after operation (6H\18H\25H);The change in hemostatic effect scores within 25 h after operation;The incidence of medically adhesive skin lesions;The anal edema score within 25 h after operation (6H\18H\25H);The anal dilatation score within 25 h after operation (6H\18H\25H);Dose of analgesics within 24 h after operation;Hospitalization costs; andLength of stay.

To assess safety, the incidence of adverse events (AEs) and severe adverse events (SAEs) between the two study groups will be compared to illustrate the potential risk to patients with nonpressure dressings after hemorrhoidectomy.

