### Statistical analysis

The validity analysis of the study will be mainly based on intention-to-treat (ITT, all randomized cases) and per-protocol analyses (PP, cases that comply with the trial protocol, good compliance, and completed CRF). First, the Shapiro-Wilk test will be used to test whether the quantitative data follow a normal distribution. If the data are normally distributed, the mean value and standard deviation will be used to describe the quantitative data, and a *t* test will be used for analysis. Nonnormally distributed data will be expressed as the median and quaternary and compared using the Mann-Whitney *U* test. The qualitative data will be expressed as the frequency and percentage; non-grade data will be compared by the chi-square test, and grade data will be compared by the Mann-Whitney *U* test. Randomization will be performed 24 h prior to the surgical intervention. Data will not be collected and analyzed for patients not undergoing surgical intervention. If the scheduled surgery is not performed, the study participant will be excluded from the clinical trial. For every patient who is excluded from the trial after randomization and before the start of the observation period (postoperative wound with or without compression), another study participant will be included to achieve the number of cases needed. The randomization sequence will continue. The next patient will not necessarily be assigned to the same group as the excluded patient. This research will continue until the required number of evaluable patients is reached. Due to complications, a very small number of patients may not be able to comply with the randomly assigned treatment. The study will not exclude these patients. All statistical tests will be two-sided, and *P* < 0.05 will be considered statistically significant. If baseline factors are inconsistent between the two groups, subgroup analysis and multivariate analysis will be considered.

In the safety analysis, Fisher’s exact test will be used to compare the incidence of AEs and SAEs by category (severity) between the two groups.

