## Discussion

Pressure dressings are commonly used and have been considered a clinical standard for wounds after mixed hemorrhoid operations in China. However, these dressings can lead to some postoperative complications, and there are few reports on improvements in wound dressing methods after hemorrhoid surgery. This study will be carried out to determine whether nonpressure bandaging can be used routinely after open hemorrhoidectomy and whether it may be considered in specific circumstances.

During the operation, the patients will be treated with general anesthesia, and the method of applying a pressure dressing is complicated, so at least two medical staff will perform wound bandaging; nonpressure dressings need only a self-adhesive foam dressing, and only one medical staff member will be needed to perform wound dressing, and the process takes less time. The nonpressure dressing method can not only reduce the workload of medical staff but also save time.

Methods to minimize bias were implemented whenever possible. Randomization was performed 24 h before surgery. Randomization ensures a statistically consistent baseline between the experimental and control groups. However, one limitation of this study is that the researchers and patients cannot be blinded to the group assignments. The blinding of patients is an important way to prevent bias, but unfortunately, this step cannot be carried out in this study. However, the observers can be blinded. Before conducting any trial-related procedures, the researcher will obtain a written informed consent from each potential research participant. Randomization will be performed with a random number table generated in Excel, and then, the patients will be assigned a group according to the order of admission.

The research plan is consistent with clinical practice to the greatest extent possible to ensure complete and trouble-free data collection. Observation indicators such as pain and anal swelling may have affected the evaluation at certain time points while the patient is sleeping. Missing data are expected in these cases, but they should be minimized. The research leader will bear full legal responsibility for the entire study and publish the data on the website of the Clinical Research Management Department of West China Hospital of Sichuan University. Anyone who needs data can contact the author.

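### Adverse events are defined as treatment-related only, so a causality judgement made after allocation filters the counts that the between-arm safety test compares.

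*Protocol article*

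**What the plan says.** The section Adverse events (AEs) {22} gives the definition: "AEs are defined as any treatment-related medical events". The rest of that sentence repeats the restriction, so relatedness is written into it twice. The abstract (Methods) sets the same limit: "Safety will be assessed with consideration of all adverse and severe adverse events related to the study treatment".

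These events are then compared between the arms. Under Secondary objectives, "the incidence of adverse events (AEs) and severe adverse events (SAEs) between the two study groups will be compared", with the stated aim of showing the potential risk of nonpressure dressings. Under Statistical analysis, Fisher's exact test "will be used to compare the incidence of AEs and SAEs by category (severity) between the two groups".

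On who knows the allocation, the Discussion says that "the researchers and patients cannot be blinded to the group assignments", and adds that observers can be blinded. The section Randomization and blinding says that patients can feel the pressure and cannot be blinded. It says that observers and statisticians are blinded, with the operators taking the dressing off before the observer's follow-up. The AE section has participants report events, a physician examine them, and the evaluations go to the principal investigator.

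**The concern.** Randomisation protects a comparison of all events in the two arms. It does not protect a comparison of events selected after allocation by a judgement that may depend on the arm. Here that judgement decides whether an event is an AE at all, so it comes before the count that Fisher's test uses.

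The judgement is also hard to make in this trial. Both arms have the same operation, anesthesia and preventive hemostatic drug, and the experimental arm differs partly by leaving pressure out. Whether a postoperative event belongs to the dressing or to the operation will often be unclear.

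At stake is the comparison that the objectives rely on to show the risk of the new dressing policy. An event judged unrelated is not an AE under this definition, so it may never be recorded as one, and a later all-cause analysis could not be relied on to recover it.

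**Working it through.** There is no plan figure to reproduce, so the check has two parts.

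**1. The chain in the text**

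- Entry condition: an event is an AE only if it is treatment-related (AE section; abstract).
- Use: AE and SAE incidence is compared between the arms (Secondary objectives), with Fisher's exact test by severity (Statistical analysis).
- Knowledge of the arm: patients report the events and are not blinded, and the Discussion says the same of researchers. The evaluations go to the principal investigator. If that is the same role as the primary investigator in Randomization and blinding, this person also opens the allocation envelopes.
- Observer blinding is described through removal of the dressing before follow-up, and removal is at 24 h (Ancillary and post-trial care). That mechanism does not cover events arising while the dressing is on.
- The article states neither an all-cause comparison nor a blinded causality assessment.

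**2. What such a filter can do (illustration)**

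Inputs from the document: 93 patients per arm (Sample size), two-sided tests at 0.05 (Statistical analysis). Assumed: the all-cause AE rate p in each arm and the share r of events called related.

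Formulas: the counted AE rate in an arm is p × r. The rejection probability is the sum over all pairs (i, j) of Bin(i; 93, p_A r_A) × Bin(j; 93, p_B r_B), taken over the pairs for which the two-sided Fisher p-value is below 0.05.

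*Equal true rates: probability of a false difference*

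| True rate, both arms | All events counted | 50% v 50% related | 40% v 60% related | 30% v 70% related |
|---|---|---|---|---|
| 20% | 0.033 | 0.028 | 0.097 (counted 8% v 12%) | 0.354 (6% v 14%) |
| 30% | 0.034 | 0.032 | 0.157 (12% v 18%) | 0.567 (9% v 21%) |
| 40% | 0.034 | 0.033 | 0.222 (16% v 24%) | 0.740 (12% v 28%) |

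Example of the arithmetic: 0.20 × 0.40 = 0.08 and 0.20 × 0.60 = 0.12.

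*True difference of 20% v 40%: probability of detecting it*

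| Share called related | Counted rates | Power |
|---|---|---|
| All events counted | 20% v 40% | 0.813 |
| 50% v 50% | 0.20 × 0.5 = 10% v 0.40 × 0.5 = 20% | 0.409 |
| 70% v 40% | 0.20 × 0.7 = 14% v 0.40 × 0.4 = 16% | 0.044 |

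Unequal attribution can thus create a difference or remove one. Equal attribution does not inflate the error rate, but in this example it halves the power.

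**The case against.** The strongest reply is that the main harms do not pass through this filter. Bleeding that needs revision surgery is a primary endpoint in the abstract and the top grade of the hemostatic scale. Urinary retention, adhesive skin injury, pain, rectal tenesmus, edema and analgesic dose are also outcomes in their own right, without the AE definition's relatedness condition. This stands, and it limits the point to the AE/SAE comparison and to harms that nobody listed in advance.

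A second reply is that a biased judge is not documented. A reader might infer that the physician who judges relatedness knows the dressing. The article does not say who makes that judgement or whether that person is blinded, and it calls the observers blinded. That inference should not be made. The definition is still a poor one without it, since it puts a causality judgement in front of the test and the article states no safeguard for that judgement.

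A third reply is that the illustration rests on assumed rates and shares. That is correct. It shows what the filter can do, not what it will do here.

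Finally, a condensed article may leave safety detail to the full protocol or the SAP. That does not answer this point: the relatedness limit is a stated rule, given in two places, and an analysis plan that followed it would inherit the filter.

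**Conclusion.** The point holds in a limited form. The definition makes relatedness the entry condition for a between-arm test. That can bias the AE/SAE comparison in either direction if attribution differs by arm, and it costs power if attribution is equal. How far this happens cannot be estimated from the document. In the assumed scenarios, the false-positive rate rises from about 0.03 to 0.10–0.22 with 40% v 60% attribution and to 0.35–0.74 with 30% v 70%.

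Two stronger readings are tempting, and the document supports neither:

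- That a bleed would be called related without pressure and surgical with it. The AE section names severe postoperative hemorrhage as a known AE of both dressings, so this is a weak example of differential attribution.
- That serious events of modest grade are left out of the SAE comparison. The article expands SAE as severe adverse event but gives no working definition, and the phrase on severity category may only describe how the tables are broken down.

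The change is worth making because it is cheap and because events not recorded as AEs may not be recoverable later.

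**What to change.** - In the AE section and the abstract, define an AE as any untoward medical event from surgery onward, whatever its cause.
- In Statistical analysis, make all-cause AEs and all-cause SAEs the Fisher comparison.
- Record relatedness and CTCAE grade for each event, and report both as separate descriptive attributes. Where feasible, have relatedness assessed by someone who does not know the arm.

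The cost is one reworded definition, a few more CRF entries and longer safety tables. Patient care does not change. The article reports recruitment as under way, so the change should be dated, and the record should show which patients were followed under each definition.

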### Auditing {23}

The ethics committee will conduct local monitoring of trial quality after the first patients have been enrolled. The Trial Management Team will meet every 3 months to check the implementation of the study, including the recruitment rate, data quality, and adverse event reporting.

### Plans for communicating important protocol amendments to relevant parties {25}

The protocol, statistical analysis plan, data safety management plan, informed consent forms, and recruitment materials have been reviewed and approved by the Ethics Committee on Biomedical Research at West China Hospital of Sichuan University. Any subsequent modifications will be submitted for review, and annual safety and progress reports will be presented. In addition, online trial registries will be updated accordingly. The data will be accessible through the research center upon reasonable request.

### Dissemination plans {31a}

The outcomes will be disseminated through peer-reviewed publications, a master’s thesis, community groups, or conference presentations. The data will be published on the website of the Clinical Research Management Department of West China Hospital of Sichuan University. Anyone who needs data can contact the author.

## Discussion

Pressure dressings are commonly used and have been considered a clinical standard for wounds after mixed hemorrhoid operations in China. However, these dressings can lead to some postoperative complications, and there are few reports on improvements in wound dressing methods after hemorrhoid surgery. This study will be carried out to determine whether nonpressure bandaging can be used routinely after open hemorrhoidectomy and whether it may be considered in specific circumstances.

During the operation, the patients will be treated with general anesthesia, and the method of applying a pressure dressing is complicated, so at least two medical staff will perform wound bandaging; nonpressure dressings need only a self-adhesive foam dressing, and only one medical staff member will be needed to perform wound dressing, and the process takes less time. The nonpressure dressing method can not only reduce the workload of medical staff but also save time.

Methods to minimize bias were implemented whenever possible. Randomization was performed 24 h before surgery. Randomization ensures a statistically consistent baseline between the experimental and control groups. However, one limitation of this study is that the researchers and patients cannot be blinded to the group assignments. The blinding of patients is an important way to prevent bias, but unfortunately, this step cannot be carried out in this study. However, the observers can be blinded. Before conducting any trial-related procedures, the researcher will obtain a written informed consent from each potential research participant. Randomization will be performed with a random number table generated in Excel, and then, the patients will be assigned a group according to the order of admission.

The research plan is consistent with clinical practice to the greatest extent possible to ensure complete and trouble-free data collection. Observation indicators such as pain and anal swelling may have affected the evaluation at certain time points while the patient is sleeping. Missing data are expected in these cases, but they should be minimized. The research leader will bear full legal responsibility for the entire study and publish the data on the website of the Clinical Research Management Department of West China Hospital of Sichuan University. Anyone who needs data can contact the author.

## Trial status

Participant recruitment is still being undertaken. Enrollment started in November 2020, and the trial is expected to be completed by December 2021.

## Abbreviations

AE: Adverse event
CI: Confidence interval
CRF: Case report forms
ITT: Intention to treat
NRS: Numerical rating scale
D: Discharge
PP: Per protocol
RCT: Randomized controlled trial
SAE: Severe adverse event
SD: Standard deviation
